### Study objectives

Primary Objective

The primary objective of the POST-RENAL Study is to compare long-term overall survival of adult patients with acute renal failure according to treatment allocation in the RENAL study.

Secondary Objectives

The secondary outcomes will include:

1. Dialysis free days (for all patients at the start of RENAL study, for patients alive at Day 28, for patients alive at Day 60 and patients alive at Day 90)
2. Time to first return to dialysis beyond Day 90 (death censored)
3. Causes of death, competing risk of dialysis/Death
4. Blood pressure and requirement for treatment for high blood pressure
5. Renal function: as measured by serum creatinine and eGFR
6. Proteinuria, as measured by urine albumin:creatinine ratio
7. Quality of life: as measured by two measures (EQ-5D and SF-12)

In this study, adverse events are likely to be extremely rare due to lack of a study intervention beyond data collection. However it is possible for adverse events to arise from the interactions required for participation in the study (eg. resulting from procedure of blood collection) and these will be reportable to the coordinating centre and local ethics committee where applicable.

1. Number of events and number and proportion of patients experienced serious adverse events

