   3. GIT
   4. Neurological
   5. Sepsis
   6. Trauma without traumatic brain injury
   7. Traumatic brain injury +/- multiple trauma
   8. Metabolic
   9. Haematological
   10. Burns
   11. Renal
   12. Other medical
9. Severe sepsis at baseline
10. APACHE III score
11. SOFA score
    1. Cardiovascular domain
    2. Respiratory domain
    3. Hepatic domain
    4. Haematologic domain

(SOFA score domains will be analyzed as continuous variables and as categorical variables divided into normal function (SOFA score 0) dysfunction (SOFA score 1-2) and failure: SOFA score 3-4).

1. Last serum urea concentration before randomization
2. Last serum creatinine concentration before randomization
3. Haematological variables
4. Biochemical variables
5. Treatment with mechanical ventilation
6. Estimated glomerular filtration rate (eGFR)
7. Presence of an estimated glomerular filtration rate (eGFR) <60 ml/min

The eGFR will be calculated using the revised modification of diet in renal disease (MDRD) equation[^9^](#_ENREF_9):

eGFR = 175 × (SCr x 0.0113)^-1.154^ × (age)^-0.203^ ×((0.742 [if female]))

SCr is serum creatinine level in micromol/L

Primary analysis

The primary outcome of mortality will be reported as a survival analysis from the time patients are randomized into the RENAL study. Survival curves and estimated median survival time and its 95% confidence interval will be generated according to the Kaplan-Meier method. Data will be censored at the time when the patient was last known to be alive or to be discharged from hospital. Log-rank test will be used to assess the difference between the two survival curves.

Multivariate Cox model will be performed to provide an adjusted long term survival curve of survivors of acute kidney injury. To determine which variables to include in the multivariate Cox model, we will run first a univariate Cox regression on each baseline variable and select variables with a p-value <= 0.01.

The number of events and the median survival (if available including 95% CI) will also be reported.

Secondary analysis

Time-to-event (Time to first return to dialysis beyond Day 90, Time-to-specific cause of death) will be analysed using the same principles as in the primary outcome. Because the two events Death and First return to dialysis are competing events, data will be censored at the time of competing event if it occurs first. Log-rank test will be used to assess the difference between the two survival curves.

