As this cause-specific analysis can potentially be biased due to the presence of different cause of death, a competing risk analysis will also be undertaken if the number of competing events (Death and return to dialysis) occurring is moderate to large (e.g. > 10%). This could typically be based on the CIF and the Gray’s test.

For binary secondary outcomes (i.e. Requirement for treatment for high blood pressure), a standard Chi-square test will be used to assess the effect of treatment. Frequencies and percentages per arm, possibly a relative risk (or odds-ratio) measuring the treatment effect and its 95% CI will also be reported along with the p-value of the chi-squared test.

Continuous secondary outcomes (i.e. time to free requirement for dialysis, Blood pressure, Renal function: as measured by serum creatinine and eGFR and Proteinuria, as measured by urine albumin:creatinine ratio) will be summarized by use of mean and standard deviation as well as quantile points at 0.25, 0.5 and 0.75 reported. Comparison in differences in mean between the two groups will be carried out using univariate/multivariate linear regression.

Quality of life: as measured by two measures (EQ-5D and SF-12)

Descriptive statistics of individual responses to the 5 EQ-5D questions and to the 12 SF-12 questions by treatment allocation will be provided. Statistics will include the difference in mean score between the two group.

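### As written, time to specific cause of death is censored at a return to dialysis beyond Day 90, so later deaths drop out of that secondary analysis

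*SAP*

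**What the plan says.** Under Secondary analysis, the SAP names both outcomes in one sentence, "Time-to-event (Time to first return to dialysis beyond Day 90, Time-to-specific cause of death) will be analysed using the same principles as in the primary", which refers back to the mortality analysis. A single censoring rule then follows: "Because the two events Death and First return to dialysis are competing events, data will be censored at the time of competing event". It applies whenever the other event comes earlier, and no exception is made for the cause-of-death outcome.

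The Study objectives section is narrower. The dialysis outcome is "Time to first return to dialysis beyond Day 90 (death censored"), which names one direction of censoring only. The next objective reads "Causes of death, competing risk of dialysis/Death" and does not confine causes of death to patients who stay off dialysis.

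The following paragraph of the Secondary analysis section recognises that differing causes of death may bias the cause-specific analysis. It then says that "a competing risk analysis will also be undertaken if the number of competing events (Death and return to dialysis) occurring is moderate to large", with more than 10% as the example and the CIF and Gray's test as the likely tools.

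For the primary outcome the rule is different: "Data will be censored at the time when the patient was last known to be alive or to be discharged from hospital". Dialysis plays no part in it. In the Tables and Figures section, Figure 1 shows survival from randomization, Figure 3 shows time to death in Day 90 survivors, and Figure 4 shows the cumulative incidence of death and of first return to dialysis.

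**The concern.** A competing event is one that prevents the event of interest. Death prevents a later return to dialysis, but a return to dialysis does not prevent death. The relation runs one way (semi-competing risks), while the SAP's rule runs both ways.

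An analyst who follows the text would censor a patient at the return to dialysis and never count the later death, whatever its cause. The quantity estimated would then be death from a given cause before any return to dialysis, which is not the listed outcome. Censoring at that point is also probably informative, since mortality after a return may well differ from mortality before it. A Kaplan-Meier curve from such data could not be read as the risk of dying from that cause.

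The cause-specific deaths would also fail to add up to the deaths in the all-cause analyses, and a reader of the report would see no reason for the gap.

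**Working it through.** **Applying the rule.** Take a patient who returns to dialysis at time t and dies at a later time u.

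- Time to first return to dialysis: event at t. Correct.
- Primary all-cause survival: death at u. Correct, as there is no censoring at dialysis.
- Time to specific cause of death: censored at t, and the death at u is lost.
- CIF and Gray's test with the SAP's pair: the first event is dialysis at t, and the death at u is again not counted. This estimates death without prior return to dialysis.

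The number of deaths lost therefore equals the number of deaths after a return to dialysis beyond Day 90.

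**Figures in the SAP.** It states no event count or power for this analysis, so there is no figure to reproduce. The cohort counts agree: 1464/1508 = 97.1% and 810/1464 = 55.3%.

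**Illustrating the size.** From the SAP: 810 Day 90 survivors and a median follow-up of 3.5 years from randomization, so T is about 3.25 years after Day 90. Everything else is assumed: the share returning to dialysis, the share dying after Day 90, and the ratio k of the death hazard after return to that before.

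With constant hazards a (return), b (death before return) and c = k × b (death after return):

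- return by T = a/(a+b) × (1 − e^(−(a+b)T))
- death without return by T = b/(a+b) × (1 − e^(−(a+b)T))
- returned and alive at T = a × (e^(−(a+b)T) − e^(−cT)) / (c − a − b)
- deaths lost = return by T − returned and alive at T

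The hazards a and b are solved to match the assumed return share and total mortality.

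*Upper example:* 10% return, 20% die, k = 4. Solving gives a = 0.0358, b = 0.0602 and c = 0.2407 per year. Returned and alive at T is 0.068, so deaths after return are 0.100 − 0.068 = 0.032. Then 810 × 0.032 = 25.9 deaths, and 0.032/0.20 = 16%.

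*Lower example:* 5% return, 20% die, k = 1. Solving gives a = 0.0176 and b = c = 0.0687. Returned and alive at T is 0.0446, so deaths after return are 0.050 − 0.0446 = 0.0054. Then 810 × 0.0054 = 4.4 deaths, and 4.4/162 = 3%.

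Deaths lost, with their share of all deaths after Day 90:

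| Return | Die after Day 90 | k = 1 | k = 2 | k = 4 |
| --- | --- | --- | --- | --- |
| 2% | 20% (162) | 1.7 (1%) | 3.2 (2%) | 5.6 (3%) |
| 2% | 40% (324) | 3.8 (1%) | 6.4 (2%) | 9.7 (3%) |
| 5% | 20% (162) | 4.4 (3%) | 8.0 (5%) | 13.5 (8%) |
| 5% | 40% (324) | 9.6 (3%) | 16.0 (5%) | 24.0 (7%) |
| 10% | 20% (162) | 8.9 (5%) | 15.7 (10%) | 25.9 (16%) |
| 10% | 40% (324) | 19.3 (6%) | 31.6 (10%) | 46.6 (14%) |

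**The case against.** **The rule may be meant for the dialysis outcome only.** It names death and dialysis, not specific causes, and the objectives give only the valid direction. That may be the intention. But the sentence follows a list that includes time to specific cause of death and makes no exception, so an analyst has no textual reason to exempt it. If the narrower scope was meant, the text should say so.

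**A first-event reading is coherent.** Return to dialysis and death before dialysis exclude each other, each may censor the other for its own hazard, and Figure 4 displays this pair. This stands for Figure 4. It does not make death before dialysis the same as time to a specific cause of death.

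**The plan already provides a competing-risk analysis.** It does, and it acknowledges the problem of differing causes of death. But that analysis is conditional and reuses the same pair of events.

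**The reach is small.** This stands. Primary survival and, by its title, Figure 3 keep the deaths after dialysis. Only one secondary analysis is affected, it has no figure of its own, and only returns beyond Day 90 matter.

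Three stronger readings are tempting and not supported:

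- *That the comparison of the randomized arms is distorted.* A log-rank test with this censoring still compares the hazard of death before return. Nothing in the SAP shows a different return rate by arm.
- *That deaths linked to kidney failure are understated most.* This is plausible, but the SAP gives no causes by dialysis status.
- *That a quarter of late deaths could be lost.* If 10% return, half of them die and only 20% die overall, then 810 × 0.10 × 0.5 = 40.5 of 162 deaths, or 25%. Mortality in the other 729 would be (162 − 40.5)/729 = 16.7%, a hazard of −ln(1 − 0.167)/3.25 = 0.056 per year. Half dying over an average 1.625 years after return needs ln 2/1.625 = 0.427 per year, roughly eight times as high. Nothing in the SAP supports that ratio.

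**Conclusion.** Wrong as written, and it should be fixed, but within one secondary analysis. The structural error follows from the wording and depends on no assumed rate: deaths after a return to dialysis beyond Day 90 leave the cause-of-death analysis, and its totals will not match the all-cause results.

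The size is uncertain. At return rates of 5-10%, about 3-16% of late deaths would be dropped; at 2%, about 1-3%, which could be negligible. These ranges assume constant hazards, 20-40% mortality after Day 90 and a hazard ratio after return of 1 to 4, none of which the SAP gives. A reader might infer that the study's main mortality result is at risk. It is not, because primary survival is not censored at dialysis.

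**What to change.** Replace the single censoring sentence in the Secondary analysis section with one rule for each outcome, for example:

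> For time to first return to dialysis beyond Day 90, death is the competing event. For time to a specific cause of death, death from any other cause is the only competing event; follow-up for death continues through any return to dialysis and is not censored there.

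Carry the same event definitions into the CIF and Gray's test paragraph. Keep Figure 4, and label it as a first-event display: return to dialysis, or death before any return to dialysis.

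The cost is a few sentences and a figure label. The Study population section already seeks dialysis requirement, date of death and cause of death for patients who died after Day 90, so no new data item is needed.

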### Tables and Figures

Table 1 : Baseline characteristic (to RENAL study patients to POST-RENAL study patients)

Table 2: Time-to-event outcomes

Table 3: Binary and continuous outcomes

Figure 1 : Kaplan Meier graph of survival time from original randomization in the RENAL

Figure 2 : Kaplan Meier graph of Time to first return to dialysis beyond Day 90 (stratified by the original randomization)

Figure 3 : Kaplan Meier graph of Time to Death for Day 90 survivors

Figure 4 : Estimates of probabilities of Death and first return-to-Dialysis based on cumulative incidence functions

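### Time to specific cause of death is put under Kaplan-Meier, and no cumulative incidence by cause is specified, although the SAP itself recognises bias from different causes of death

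*SAP*

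**What the plan says.** In the SAP, Study objectives, the third secondary outcome is "Causes of death, competing risk of dialysis/Death".

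Under Statistical analysis, Secondary analysis, two time-to-event outcomes are named: first return to dialysis, and death by cause. The method comes by cross-reference: "Time-to-specific cause of death) will be analysed using the same principles as in the primary outcome". Those principles stand under Primary analysis: "Survival curves and estimated median survival time and its 95% confidence interval will be generated according to the Kaplan-Meier method", with censoring when the patient was last known to be alive or discharged, and a log-rank test.

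One explicit rule for competing events follows: "Because the two events Death and First return to dialysis are competing events, data will be censored at the time of competing event", if that event comes first. It concerns death against dialysis. No rule is stated for a death from a cause other than the one being analysed.

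The next paragraph opens: "As this cause-specific analysis can potentially be biased due to the presence of different cause of death". The same sentence then makes the remedy conditional: "a competing risk analysis will also be undertaken if the number of competing events (Death and return to dialysis) occurring is moderate to large", with more than 10% given as an example. The cumulative incidence function and Gray's test are suggested as the typical basis.

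Under Tables and Figures, the only cumulative incidence output is Figure 4: "Estimates of probabilities of Death and first return-to-Dialysis based on cumulative incidence functions".

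**The concern.** A patient who dies of one cause can no longer die of another. Kaplan-Meier applied to a single cause has only one place for such a patient: censored at death, as though still at risk of the cause of interest. One minus Kaplan-Meier then estimates the risk that would apply if the other causes did not exist (and were independent of this one). It does not estimate the proportion of patients who die of that cause.

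The SAP's reason for a competing-risk analysis is bias from different causes of death, but the events it names and the figure it plans treat death as one pooled event. A cumulative incidence function for all-cause death against dialysis says nothing about the risk of each cause. An analyst who follows the text closely could therefore run the competing-risk analysis in full and still have only Kaplan-Meier estimates by cause.

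At stake is a listed secondary outcome in a study whose purpose is to describe long-term outcomes. Risks by cause that add up to more than the all-cause mortality in the primary analysis would be visibly inconsistent.

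**Working it through.** **Inputs from the SAP (Study population).** 1508 randomized, 1464 with a known Day-90 outcome, 810 alive at Day 90. Check: 1464/1508 = 97.1% and 810/1464 = 55.3%, which agree with the stated 97.1% and 55%. Day-90 mortality is therefore (1464 − 810)/1464 = 654/1464 = 44.7%. The SAP states no event count, power or expected risk for the by-cause analysis, so there is no planned figure to reproduce.

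**Assumptions.** The SAP gives neither mortality after Day 90 nor a split by cause. I take all-cause mortality *F* of 20%, 30% and 40% in Day-90 survivors. One cause takes a share *s* of the hazard, from 10% to 75%. Cause-specific hazards are proportional, and there is no other censoring.

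**Formulas.**
- One minus Kaplan-Meier, with other causes censored: 1 − (1 − *F*)^*s*
- Cumulative incidence (CIF): *s* × *F*
- Standard error of the latter: √[CIF(1 − CIF)/*n*]

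For example, with *F* = 0.30 and *s* = 0.40, 1 − 0.70^0.40 = 13.3%, against 0.40 × 0.30 = 12.0%. The excess is 1.3 points. The standard error at *n* = 810 is √(0.12 × 0.88/810) = 1.14 points, so the excess is 1.1 SE.

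**Day-90 survivors, *n* = 810.**

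| *F* | *s* | 1 − KM | CIF | Excess (points) | Excess / SE |
|---|---|---|---|---|---|
| 20% | 10% | 2.2% | 2.0% | 0.2 | 0.42 |
| 20% | 50% | 10.6% | 10.0% | 0.6 | 0.53 |
| 20% | 75% | 15.4% | 15.0% | 0.4 | 0.33 |
| 30% | 25% | 8.5% | 7.5% | 1.0 | 1.11 |
| 30% | 50% | 16.3% | 15.0% | 1.3 | 1.06 |
| 40% | 25% | 12.0% | 10.0% | 2.0 | 1.89 |
| 40% | 50% | 22.5% | 20.0% | 2.5 | 1.81 |

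**Sum over four causes** (shares 40/30/20/10%): the one-minus-Kaplan-Meier values add to 21.6% when *F* = 20%, 33.8% when *F* = 30% and 47.4% when *F* = 40%. The cumulative incidences add to *F* exactly.

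**Simulation check** (200,000 patients, *F* = 30%, the same four causes): 13.4, 10.1, 7.0 and 3.5% by one minus Kaplan-Meier, against 12.1, 9.0, 6.1 and 3.0% by cumulative incidence. This agrees with the formulas.

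**Timed from randomization.** This is the origin of the primary analysis. At the SAP's own Day-90 mortality of 44.7%, a cause with half the hazard gives 1 − 0.553^0.5 = 25.6% against 22.3%, an excess of 3.3 points. Over shares of 10% to 75% the excess is 1.3 to 3.3 points. At an assumed 55–70% mortality by the end of follow-up it is about 2 to 10 points. These figures apply only if causes are known for deaths before Day 90.

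**The case against.** The strongest reply is that the SAP names this very problem and answers it in the same sentence: bias from different causes of death is the stated reason for a competing-risk analysis with cumulative incidence and Gray's test. The parenthesis naming death and return to dialysis sits inside the condition that triggers the analysis, and need not limit its scope. This stands in part. A reader might infer that the SAP rules out cumulative incidence by cause, and the text does not say that. What it does is leave such an analysis unspecified: no sentence, table or figure calls for it, and the only events named as competing do not match the reason given.

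Further points stand:

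- Censoring of other-cause deaths is implied by the cross-reference to Kaplan-Meier and by the label cause-specific. It is not stated.
- The log-rank test with other causes censored is a valid comparison of cause-specific hazards, so it would be wrong to infer that the planned comparison between arms is invalid.
- No Kaplan-Meier figure by cause is listed, and the contents of Table 2 (time-to-event outcomes) are not itemised. The overstatement arises only if one minus Kaplan-Meier is reported and read as absolute risk.
- Medians by cause are unlikely to matter. They are reported only if available, and no by-cause curve reaches 50% in the Day-90-survivor scenarios.
- The size rests on assumed rates. Measured against a single arm's precision it shrinks: with an assumed 405 survivors per arm, the 0.53 SE at 20% mortality and a 50% share becomes 0.37 SE.
- The larger figures from randomization need causes for deaths before Day 90. Under Study population, the SAP says cause of death will be sought for patients who died beyond the 90-day follow-up. It does not show that earlier causes are available.

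**Conclusion.** The point holds as a gap in specification with a known direction of bias. The SAP assigns an estimator to time to specific cause of death that does not give absolute risk when other causes compete. Its conditional remedy names events that do not address the cause-of-death endpoint.

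One minus Kaplan-Meier by cause is never below the cumulative incidence, and exceeds it once earlier deaths from other causes have occurred. In Day-90 survivors the excess is modest: about 0.2 to 2.5 percentage points per cause at an assumed 20–40% mortality with cause shares of 10–75%. In some 20% scenarios it is under half a standard error even for the whole cohort. A reader might infer a material distortion in every case, but the figures do not support that. The larger excess from randomization is conditional on data that the SAP does not promise.

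The primary analysis and the log-rank comparisons of cause-specific hazards are unaffected. The point concerns the description of absolute risk within one secondary outcome, and it is worth correcting because the correction is cheap.

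**What to change.** In the SAP, Secondary analysis:

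1. State that, for each cause-of-death category, deaths from all other causes are competing events.
2. Report the absolute risk of each cause by its cumulative incidence function, with Gray's test to compare these functions between arms. Do not make this depend on the 10% condition.
3. Keep the log-rank test, described as a test of the cause-specific hazard.
4. Keep Figure 4 as it is for death against return to dialysis, and add one table or figure of cumulative incidence by cause beside all-cause mortality, so that the two can be seen to agree.

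The cost is a few sentences of wording and one extra table or figure. For deaths after Day 90 no new data are needed, since date and cause of death are already sought. If the analysis is to start at randomization, the SAP should also say whether causes of earlier deaths are available. The only visible effect on results is that the reported risks by cause become slightly smaller.

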### Tables and Figures

Table 1 : Baseline characteristic (to RENAL study patients to POST-RENAL study patients)

Table 2: Time-to-event outcomes

Table 3: Binary and continuous outcomes

Figure 1 : Kaplan Meier graph of survival time from original randomization in the RENAL

Figure 2 : Kaplan Meier graph of Time to first return to dialysis beyond Day 90 (stratified by the original randomization)

Figure 3 : Kaplan Meier graph of Time to Death for Day 90 survivors

Figure 4 : Estimates of probabilities of Death and first return-to-Dialysis based on cumulative incidence functions

